## Abstract

The survival rates for children with cancer have increased appreciably over the last few decades; however, childhood cancer survivors continue to suffer from long-lasting sequelae. Studies have demonstrated that the presence of malnutrition, over- and under-nutrition, at diagnosis or the duration of malnutrition during treatment is associated with increased toxicity, infection, and inferior survival. Dietary habits, along with behavioral and socioeconomic status, are known factors that lead to obesity or undernutrition and can affect the prognosis and quality of life of children with cancer. Unfortunately, the underlying mechanisms responsible for these observations are largely unknown. To address this gap in science, we established the EPIC*kids* cohort study, an initiative of the International Initiative for Pediatrics and Nutrition at Columbia University Irving Medical Center and the International Agency for Research on Cancer of the World Health Organization. Over a 5-year period, children and adolescents with acute lymphoblastic leukemia and brain tumors receiving treatment in Spain, Italy, or Greece will be recruited. Clinical data and biospecimens (blood and stool) will be collected at designated timepoints in therapy. At the same time, several surveys will be administered to collect data on sociodemographics, physical activity, quality of life, food insecurity, and dietary habits. The primary aim of EPIC*kids* is to develop a large informative nutrition biobank and database to investigate the etiologic pathways that connect nutritional status and lifestyle factors with clinical outcomes in children and adolescents with cancer. Secondary aims are to create evidence-based guidelines for European children with cancer in this understudied region and to ultimately improve the quality of life of those children and adolescents.

The ClinicalTrials.gov ID for EPIC*kids* study is NCT05375617.

## Introduction

Every year, nearly 400,000 children and adolescents (0–19 years of age) are diagnosed with cancer worldwide. Leukemias and brain tumors are the most common types of cancer, with more than 80% of children with cancer cured in high-income countries (HICs). [1,2] Despite these accomplishments, the development of malnutrition (both over- and undernutrition) and nutrition-related conditions (e.g., metabolic syndrome, pancreatitis) predisposes children to adverse events during and after cancer care and negatively impact quality of life and survival. [3]

In children with acute lymphoblastic leukemia (ALL), several investigations have reported that poor nutritional status and dietary intake adversely impact prognosis and increase the incidence of several treatment-related toxicities. [4] Specifically, 5-year event-free survival was observed to be 64% and 65% for children with obesity or underweight at diagnosis, respectively, compared to 74% for those with a healthy weight (*P* = 0.002). [5] Obesity has consistently been associated with increased toxicities and inferior survival [6], which may be due to challenges with optimal drug dosing since increased adiposity may affect the pharmacokinetics and dynamics of lipophilic drugs. [7] Similarly, undernutrition is associated with numerous deleterious outcomes, such as reduced tolerance to treatment, increased toxicity, and infection. [3,8–11] Up to 70% of children and adolescents with ALL develop overweight/obesity by the end of treatment in the United States. [12] Obesity has been a risk factor for metabolic syndrome [13], hyperglycemia [14], pancreatitis and hepatotoxicity in children with cancer. [6,15]

Children with brain tumors face similar challenges related to nutrition, although much less data is available. Undernutrition has been observed in 31% of children with medulloblastoma and other aggressive tumors at diagnosis [16], and it has been reported that up to 94% of children with medulloblastoma and 39% of children with other central nervous system tumors develop undernutrition during treatment. [17] Further, approximately 40% of children with brain tumors experience swallowing difficulties [18,19], which contribute to decreased oral intake and further decline in nutritional status. At the same time, the development of overweight/obesity is commonly observed in children and adolescents with hypothalamic damage due to radiation therapy, surgery, or by the tumor itself [20], resulting in endocrinopathies such as diabetes insipidus and central precocious puberty. [21] In one of the few reported European cohorts of survivors of a childhood brain tumor, a higher prevalence of overweight/obesity was observed as compared to the general population (29% compared to 13%, respectively) [21] as well as a greater percent of fat mass compared to non-cancer controls (mean difference 4.1%, 95% confidence interval 2.0–6.1). [22]

More recently, it has been reported that the duration of “aberrant nutritional status” (the time at which children are in an ‘at-risk’ nutrition state during treatment) appears to be more consistently associated with poor clinical outcomes. [5,23] However, the mechanisms by which nutrition impacts these outcomes are largely unknown. [24] Genetic predisposition [25,26], microbial environment [6] or parental feeding behaviors [27] may be responsible for excess weight gain. In children with ALL, remission induction therapy significantly reduces bacterial diversity in the gut and may contribute to the development of obesogenic microbial profiles. [28] The frequent use of antibiotic therapy during the induction phase of therapy causes additional insult to the intestinal microbiota, further augmenting this phenotype. [29] Unfortunately, much of the existing data are in children with ALL, with little information on the underlying mechanisms in children with brain tumors. Moreover, most findings are limited to children residing in North America.

Whether these findings are relevant to the European setting is unknown, given variations in treatment, lifestyle, environmental exposures, and the gut microbiome/metabolome. Studies have found that the Mediterranean diet and lifestyle are associated with reduced side effects of treatment, improved quality of life, and lower risk of adult-onset cancer. [30,31] The relevance in the pediatric setting is unknown. To address this gap in science, we established the Southern **E**uropean **P**rospective **I**nvestigation Into **C**hildhood Cancer and Nutrition (EPIC*kids*), which addresses this understudied area and establishes a novel infrastructure to comprehensively examine diet, lifestyle, and biological parameters among children and adolescents diagnosed with the two most common forms of childhood cancer.

## Materials and methods

### Study design

The EPIC*kids* study (clinicaltrials.gov NCT05375617) is a prospective, observational, multinational cohort study recruiting children and adolescents with newly diagnosed ALL or favorable biology brain tumors and following participants from diagnosis until 1-year after the end of treatment (EOT). Recruitment began in June of 2023 and will continue through December 2028. Completion of the study is expected in January 2031, with analysis anticipated to be performed upon study completion. EPIC*kids* is being co-led by the International Initiative for Pediatrics and Nutrition (IIPAN), Columbia University Irving Medical Center (CUIMC) and the International Agency for Research on Cancer/World Health Organization (IARC/WHO).

Eligible participants are children and adolescents diagnosed with ALL meeting the following criteria: (1) aged between 3 and 21 years old at diagnosis with B-cell ALL, T-cell ALL, or mixed phenotype acute leukemia confirmed on immunophenotyping by flow cytometry and receiving standard leukemia treatment at one of the participating centers or may be children on a clinical trial or “as per” a clinical trial. For the brain tumor cohort, eligible children are: (1) aged between 3 years and 21 years old at the time of diagnosis with a favorable biology brain tumor (tumors with expected 5-year survival > 70%) confirmed by either pathology report, imaging and/or biochemical studies including low-grade gliomas, some medulloblastomas, ependymomas, pituitary tumors, germ cell tumors, and (2) receiving standard treatment at one of the participating centers with surgery, chemotherapy, radiation therapy or may be children on a clinical trial or “as per*”* a clinical trial. Children receiving autologous stem cell transplantation as part of their regimen may be included. Participating centers enrolling children and adolescents are listed in Table 1.

**Table 1 pone.0319110.t001:** Participating centers in EPIC*kids* cohort.

Institution Name	Location
Aghia Sofia Children’s Hospital	Athens, Greece
Fondazione IRCCS San Gerardo dei Tintori	Monza, Italy
Fondazione IRCCS Istituto Nazionale dei Tumori	Milan, Italy
Hospital Vall D’Hebrón	Barcelona, Spain
Pediatric Cancer Center Barcelona, Hospital Sant Joan de Déu	Barcelona, Spain
Hospital Infantil Universitario Niño Jesús	Madrid, Spain
Hospital Universitario La Paz	Madrid, Spain
Hospital Universitario Virgen del Rocío	Seville, Spain

Each participating institution has a dedicated research assistant for the study, an institutional principal investigator (PI), and laboratory space for processing and storage of all stool and blood specimens. The biobank for all biological samples is centralized at IARC in Lyon, France, while the corresponding clinical data are managed by the IIPAN research team at CUIMC, New York, United States, using a REDCap database.

The primary aim of this study is to establish an informational resource on critical parameters of nutrition by which we can describe the trajectory of nutritional status among Southern European children and adolescents with ALL and favorable biology brain tumors, investigate lifestyle behaviors, sociodemographic factors, quality of life, and the intestinal microbiome/metabolome, and correlate these indicators with clinical outcomes.

### Clinical data collection

Initial and final risk groups and Grade 3 or 4 nutrition-related treatment-related toxicities (TRT) as defined by the National Cancer Institute Common Terminology Criteria for Adverse Events (CTCAE, version 5.0) will be abstracted from the medical records and input into the study’s REDCap database. The TRT that will be collected include all new cases of infection, mucositis, bone fractures, pancreatitis, hyperglycemia, liver toxicity, and peripheral neuropathy. Survival and clinical outcomes will be defined by uniform standards of practice in pediatric oncology: treatment-related mortality (TRM, death due to toxicity related to therapy), event-free survival (EFS, time from diagnosis to induction failure, relapse, secondary malignancy, or death), overall survival (OS, time from enrollment to death from any cause), and cumulative incidence of relapse (CIR, time to post-remission relapse). The number of days of hospitalization will also be collected. Administration of selected medications (e.g., steroids and antimicrobials) strongly associated with nutritional status or the microbiome will be collected prospectively. For participants receiving radiation therapy, information about the total dose and area/volume radiated will be collected. For the brain tumor cohort, information on pre-existing or newly developed endocrinopathies will be collected at each timepoint including growth hormone deficiency, pubertal delay, precocious puberty, hypogonadism, hypopituitarism, hypothyroidism, adrenocorticotropic hormone deficiency, and diabetes (type 2 diabetes mellitus or diabetes insipidus).

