### Statistical analysis

The study protocol aims to describe the establishment of the infrastructure for this multi-national collaboration. There are no statistical considerations for this study. Over five years, we propose to recruit 900 children and adolescents with newly diagnosed ALL and 1,400 children and adolescents with newly diagnosed brain tumors. This study will provide the opportunity for hypothesis-driven research proposals, which will be submitted separately. Individual investigators are responsible for biostatistical planning in study design and outcome assessments according to the needs of specific projects. Based on current the average incidence of overweight/obesity (~30%), underweight (~10%), and treatment-related toxicities (range 5–40%), we will have 80% power when comparing groups*.*

Although this cohort study aims to collect clinical information and biospecimens from children undergoing cancer therapy to establish an information resource to address research questions yet to be defined, some basic analyses have been established a priori. Clinical data abstracted from the medical charts will be integrated with biological data. Metagenomic sequencing will be employed on stool specimens to provide information on taxonomic composition, microbial diversity and richness, and host-microbiome pathways analysis. Blood specimens will be utilized to examine genetic predispositions to nutrition conditions, nutrient analysis, and and the metabolome. Composition and diversity of the microbiome will be evaluated within the context of nutritional outcomes, treatment-related toxicities, and survival, controlling for confounding variables such as type of disease and lifestyle variables. We will also evaluate the microbiome with metabolic profiles and examine their association with similar clinical outcomes. Dietary intake will be corroborated in a subset of participants through analysis of serum micronutrient values. Finally, all analytical approaches will consider confounding variables (e.g., type of ALL or brain tumor, demographic and clinical charactersitics) using directed acyclic graphs.

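### The single event-free survival definition lists no tumour progression, so growth of residual brain tumour is not a failure as written

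*Protocol article*

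**What the plan says.** Under Clinical data collection the article introduces its outcomes with "Survival and clinical outcomes will be defined by uniform standards of practice in pediatric oncology" and then spells each one out. Event-free survival is "event-free survival (EFS, time from diagnosis to induction failure, relapse, secondary malignancy, or death". The relapse outcome is "cumulative incidence of relapse (CIR, time to post-remission relapse". Overall survival is "overall survival (OS, time from enrollment to death from any cause". No separate version of any of these is given for the brain-tumour cohort, although the same section does add cohort-specific text on endocrinopathies for those children.

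Under Study design, the brain-tumour cohort covers favourable-biology tumours, "including low-grade gliomas, some medulloblastomas, ependymomas, pituitary tumors, germ cell tumors". Confirmation may come from pathology, imaging or biochemistry. In Table 3 the first brain-tumour collection follows surgery or biopsy and precedes chemotherapy or radiation. The recruitment target, under Statistical analysis, is: "we propose to recruit 900 children and adolescents with newly diagnosed ALL and 1,400 children and adolescents with newly diagnosed brain tumors".

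**The concern.** A brain tumour that is biopsied, partly resected or diagnosed on imaging can remain in place. For such a child a natural form of treatment failure is growth of that tumour. The written event list has no term for it, and an outcome restricted to relapse after remission does not cover it either.

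The study says it will use these outcomes. The primary aim under Study design correlates nutritional indicators with clinical outcomes, the Statistical analysis section plans to relate the microbiome to survival, and the last of the six listed research questions asks how nutritional indicators relate to survival. If progression is left out, or recorded by some sites as relapse and by others not at all, event-free survival in the brain-tumour cohort would not mean the same thing across eight centres in three countries.

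**Working it through.** **Share of the sample.** Inputs are the two recruitment targets under Statistical analysis. Total = 900 + 1,400 = 2,300. Brain-tumour share = 1,400 / 2,300 = 0.609, or 60.9%. The article states no event rate, event count or sample-size result for event-free survival, so there is no figure of its own to reproduce on this point.

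**Written events applied to a child with residual tumour and no remission.**

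| Listed event | Does growth of residual tumour meet it? |
|---|---|
| Induction failure | No; this is a leukemia treatment term |
| Relapse | Not on the plain wording, since no remission or clearance came first; a site might still code it so |
| Second cancer | No |
| Death | Only if and when the child dies |

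The relapse outcome is explicitly conditional on remission, so a child who never has one cannot have the event.

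**Can such children be enrolled?** Yes. Confirmation by imaging is allowed, and the first collection may follow a biopsy. Neither requires that the tumour has been removed.

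**Direction of the error.** Let T_w be the time to the first listed event, P the time to progression, and T_f = min(P, T_w) the time to the first event once progression is added. Then T_f ≤ T_w for every child, so the event-free proportion under the written list is at least as high as under the full list at every time point. It is strictly higher once any child progresses before a listed event. This needs no assumed rate.

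**Size.** If a fraction q of the brain-tumour cohort progresses during follow-up without a listed event, the number missed is 1,400 × q, which is 14 children for each percentage point. The article gives neither q nor the proportion with residual tumour, so the number itself cannot be computed. If some sites code progression as relapse, fewer are missed, but the definition then differs by site.

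**The case against.** The strongest reply is that this is a resource-building study. Its main product is a biobank and database, the article says there are no statistical considerations, and later projects are to specify their own outcome assessments. No sample size or decision rests on event-free survival. Clinical data are collected at each timepoint, so progression may already be in the chart and perhaps on the data form, which is not shown. A condensed article may also leave event coding to the full protocol. This limits the consequence: it is a faulty definition, not demonstrated loss of data. It does not remove the fault, because the article does not leave the events open. It lists them, and the appeal to uniform standards does not override a written list.

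Several stronger readings are tempting and are not supported:

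- *That the list contains leukemia events only.* Only induction failure is specific to leukemia. Relapse, second cancer and death can all occur, and are counted, in a child with a brain tumour.
- *That 61% of failures are lost.* That figure is the cohort's share of planned participants. Recurrence after complete resection, second cancers and deaths are still countable.
- *That fatal toxicity is missing because toxicity is limited to* "Grade 3 or 4 nutrition-related treatment-related toxicities (TRT". The same section collects "treatment-related mortality (TRM, death due to toxicity related to therapy", and those deaths also count in event-free and overall survival. At most, the text does not say whether a fatal toxicity is also tallied under its own toxicity type.
- *That associations with nutrition would be diluted.* This is not shown. Missing events at the same rate in all groups costs precision but does not by itself pull a risk ratio towards no effect.

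**Conclusion.** The point holds in this form: the event-free survival definition, shared by both cohorts, omits tumour progression, and the relapse outcome is confined to relapse after remission. For brain-tumour children with tumour left in place, progression without prior remission is not an event until another listed event occurs, and these children fall outside the relapse outcome. Event-free survival in the brain-tumour cohort would be overstated or coded inconsistently between sites. The direction follows from the definition and needs only that some such children progress. The size cannot be derived from the article. A reader might infer that event-free survival would nearly coincide with overall survival in this cohort, but that would need progression and relapse rates that the article does not give. The definition matters because the cohort makes up 60.9% of planned recruitment and survival is among the outcomes to be analysed.

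**What to change.** Leave the leukemia definitions as they are. For the brain-tumour cohort:

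1. Define event-free survival as time from diagnosis to the first of progression or recurrence, second cancer, or death from any cause.
2. Replace the relapse outcome with the cumulative incidence of progression or recurrence, treating death as a competing event.
3. Check that the data form can record progression and its date, distinct from relapse, and add the option if it cannot.

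The cost is a wording change and possibly one form option. The form is not shown, so progression may already be recordable. Records already entered would need review: 72 children had been recruited at the time of writing, and under Data monitoring and quality control forms are locked after verification with no later changes. The change is therefore cheaper the earlier it is made.

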### Collection of biological specimens

An overview of the collection of biological specimens for the ALL and brain tumor cohorts is provided in Tables 2 and 3. For children with ALL, blood and stool will be collected at five timepoints (at diagnosis, at the end of induction, at the beginning of maintenance, at the end of treatment and 1 year after the end of therapy) representing times in which fluctuations in nutritional status have been reported. For the brain tumor cohort, the initial collection is after surgery, with further collections at 3-month intervals until one year after the end of treatment. Blood samples are obtained during a routine blood draw in serum separator tubes, centrifuged, and stored at −80°C until shipped for long-term storage at IARC. Stool samples are collected in the hospital or the home setting using a specified protocol. The collected stool is stored on fecal occult blood test cards and cryovials until shipped for long-term storage at IARC.

**Table 2 pone.0319110.t002:** Summary of data collection: acute lymphoblastic leukemia cohort.

	Timepoint 1	Timepoint 2	Timepoint 3	Timepoint 4	Timepoint 5
	Diagnosis	End of induction	Beginning of Maintenance	End of Treatment	1 Year Post-End of Treatment
Timepoint window	Collect ± three working days	Collect ± three working days	Collect ± one month	Collect ± one month	Collect ± one month
STUDY INSTRUMENTS					
Demographics survey: WHO World Health Survey	x		x	x	
Food security survey: FIES	x				
Quality of life survey: PedsQL	x	x	x	x	x
Physical activity survey: PROMIS	x	x	x	x	x
Dietary data: Food Frequency Questionnaire and Nutrition support form	x	x	x	x	x
MEDICAL DATA					
Clinical data and disease characteristics	x	x	x	x	x
Anthropometrics: height, weight, MUAC	x	x	x	x	x
BIOLOGICAL SAMPLES					
Blood collection	x	x	x	x	x
Stool collection	x	x	x	x	x

*Abbreviations*: WHO, World Health Organization; FIES, Food Insecurity Experience Scale; PedsQL, Pediatric Quality of Life; PROMIS, Patient Reported Outcome Measurement Information System; MUAC, mid-upper arm circumference

**Table 3 pone.0319110.t003:** Summary of data collection: brain tumor cohort.

	Timepoint 1	Timepoints 2–8	Timepoint EOT	Timepoint EOS
	Diagnosis or Post-surgery	Repeat every 3 months from timepoint 1 until the end of treatment	End of treatment	End of Study, 1 Year Post-End of Treatment

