Timepoint window	Collect after surgery/biopsy but prior to initiation of chemotherapy or radiation	Collect ± 14 days	Collect ± 14 days	Collect ± 1 month
STUDY INSTRUMENTS				
Demographics survey: WHO World Health Survey	x		x	x
Food security survey: FIES	x			
Quality of life survey: PedsQL	x	x	x	x
Physical activity survey: PROMIS	x	x	x	x
Dietary data: Food Frequency Questionnaire and Nutrition support form	x	x	x	x
MEDICAL DATA				
Clinical data and disease characteristics	x	x	x	x
Anthropometrics: height, weight, MUAC	x	x	x	x
BIOLOGICAL SAMPLES				
Blood collection	x	x	x	x
Stool collection	x	x	x	x

*Abbreviations*: EOT, end of treatment; EOS, end of study; WHO, World Health Organization; FIES, Food Insecurity Experience Scale; PedsQL, Pediatric Quality of Life; PROMIS, Patient Reported Outcome Measurement Information System; MUAC, mid-upper arm circumference

Participating institutions will batch ship blood and stool specimens yearly, sending only those from participants who have completed the study to IARC for biobanking. Prior to shipping, packaging will be inspected for contamination and humidity cards will be replaced along with dessicant packs, if indicated by the indicator located on the humidity cards. Specimens will be shipped on dry ice using an overnight courier that can properly handle biological specimens and has an established collaboration with IARC.

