We anticipate utilizing these data to estimate the power and sample size needed for future intervention studies, as well as answer some basic research questions such as: 1) How does dietary intake fluctuate during and after treatment for ALL or a brain tumor?; 2) What is the effect of treatment on nutritional status, defined by anthropometric measures (severely underweight, underweight, healthy weight, overweight, or obese) at baseline and at follow-up assessments? 3) What is the association between poor quality of life and nutritional status over the course of treatment? 4) What are the associations between food security, nutritional status (anthropometric), dietary intake, and treatment-related toxicities? 5) What are the overall trends of the aforementioned nutritional indicators and determinants (dietary intake, nutritional status, HRQOL, socioeconomic status) during the course of therapy? and 6) How are these nutritional indicators associated with survival in children with cancer? These analyses will allow the researchers and staff members to develop lifestyle interventions that may be tested through controlled, randomized trials to further improve outcomes among children with cancer.

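### Overall survival is timed from enrollment but event-free survival from diagnosis, so a child whose first event is death can have EFS longer than OS

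*Protocol article*

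**What the plan says.** The protocol article, Clinical data collection, lists the survival outcomes in one sentence. It opens with "Survival and clinical outcomes will be defined by uniform standards of practice in pediatric oncology". It then gives "event-free survival (EFS, time from diagnosis to induction failure, relapse, secondary malignancy, or death" and, next to it, "overall survival (OS, time from enrollment to death from any cause". EFS therefore starts at diagnosis and OS at enrollment.

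Study design describes the cohort as "recruiting children and adolescents with newly diagnosed ALL or favorable biology brain tumors and following participants from diagnosis until 1-year after the end of treatment". Children already have their diagnosis when recruited, so enrollment is on or after the diagnosis date. Follow-up is described as running from diagnosis, which agrees with the EFS origin and not with the OS origin.

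The article gives no interval from diagnosis to enrollment. The nearest information is the window for the first data collection. For acute lymphoblastic leukemia (ALL, Table 2) it is "Collect ± three working days" around diagnosis. For brain tumors (Table 3) it is "Collect after surgery/biopsy but prior to initiation of chemotherapy or radiation", with no limit in days.

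Statistical analysis lists, among the questions the data should answer, "How are these nutritional indicators associated with survival in children with cancer". It leaves biostatistical planning for each project to the investigators who propose it.

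**The concern.** Death is an event for both endpoints, so a child's EFS time should never exceed the OS time. With two time zeros that ordering can fail, and the EFS and OS curves cannot be read against each other at a given time since diagnosis.

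There is a second, conditional consequence. A child must be alive to enroll. If EFS is counted from diagnosis and the child is treated as at risk from that day, the stretch before enrollment is event-free by selection and early EFS is overstated.

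The definitions sit in the shared protocol of a resource meant to serve many separate projects. Each project that takes its endpoints from here inherits the mismatch.

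**Working it through.** The article states no event count, power or sample size that depends on these origins, so there is no figure of its own to reproduce. Two checks apply.

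**1. Ordering of the two times.** Let a child die on day D after diagnosis with no earlier EFS event, and let enrollment be g days after diagnosis. From the two definitions:

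- EFS = D
- OS = D − g
- EFS − OS = g

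For a death on day 180:

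| Gap g (days, assumed) | EFS | OS | EFS − OS |
|---|---|---|---|
| 0 | 180 | 180 | 0 |
| 5 | 180 | 175 | 5 |
| 14 | 180 | 166 | 14 |
| 30 | 180 | 150 | 30 |
| 90 | 180 | 90 | 90 |

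The ordering fails by exactly g whenever g is above zero. With one common origin the difference is 0 for such a child, and EFS cannot exceed OS for anyone.

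**2. Size of the bias if delayed entry is omitted.** The inputs are:

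- 5-year EFS from the Introduction, for a cited ALL study: "5-year event-free survival was observed to be 64% and 65% for children with obesity or underweight at diagnosis, respectively, compared to 74" percent. I use 74% (healthy weight) and 64% (obesity).
- Gap g: not given, so assumed at 5 to 90 days. Three working days across a weekend are about 5 calendar days, which is the ALL case. The longer values illustrate a window with no limit in days.
- Constant hazard: assumed.

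The hazard is λ = −ln(S5)/5. That is 0.0602 per year at 74% and 0.0893 per year at 64%. Among children who reach enrollment event-free, 5-year EFS counted from diagnosis without delayed entry is S5 / exp(−λg), with g in years. The overstatement is that value minus S5.

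| Gap g | Points over 74% | Points over 64% |
|---|---|---|
| 5 days | 0.06 | 0.08 |
| 14 days | 0.17 | 0.22 |
| 30 days | 0.37 | 0.47 |
| 56 days | 0.69 | 0.88 |
| 90 days | 1.11 | 1.42 |

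Worked line for 56 days at 74%: g = 56/365.25 = 0.1533 years; λg = 0.0602 × 0.1533 = 0.00923; 0.74 × exp(0.00923) = 0.7469; overstatement 0.69 points.

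If both weight groups have the same gap, their 10-point difference (74 − 64) shrinks by 0.22 − 0.17 = 0.05 points at 14 days and by 1.42 − 1.11 = 0.31 points at 90 days.

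**The case against.** The best reply is that little follows in practice. The article specifies no survival analysis. It leaves that to separate projects, and an analyst who uses delayed entry has no bias from pre-enrollment time. The absence of a delayed-entry statement is a matter for an analysis plan and is not a defect here. The gap may also be near zero. Study procedures puts consent before collection, so the collection windows only bound enrollment from above. Table 3 labels the first brain tumor timepoint as diagnosis or post-surgery, and a pathology diagnosis may itself be dated close to surgery or biopsy. Survival has no stated test.

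All of that stands, and it limits the size. It does not remove the mismatch, because the article itself fixes both origins.

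A reader might infer more than the documents support:

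- **That EFS as planned is already biased upward.** This holds only if delayed entry is omitted, and the article does not say either way.
- **That contrasts between ALL and brain tumors, or between countries, carry an artefact.** No such survival contrast is planned. Disease type is named as a confounder to control, and the listed survival question concerns nutritional indicators. A gap that is alike across nutritional groups changes their difference very little, and nothing shows that it differs.
- **That the lost interval is the peak period for deaths from treatment toxicity.** The brain tumor window closes before chemotherapy or radiation starts, so deaths from those treatments cannot fall in it. Deaths around surgery could, but the documents give no rate.

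**Conclusion.** The point holds as an inconsistency in stated definitions. EFS and OS have different time zeros, and a first-event death then gives EFS longer than OS by the interval from diagnosis to enrollment. The only case in which this disappears is enrollment on the day of diagnosis, which the article does not say.

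The numerical effect is probably small. It is likely negligible for ALL, where the baseline window suggests a gap of a few days. It may be larger for brain tumors, where the window has no limit in days and a child treated by surgery alone has no later treatment start to close it. Brain tumors are also the larger planned cohort, 1,400 of 900 + 1,400 = 2,300.

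The bias figures rest on assumed gaps, a constant hazard, survival figures from an ALL study applied as illustration, and omission of delayed entry. A higher early hazard would raise them. The inconsistency in the definitions rests on none of these.

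**What to change.** Give EFS and OS the same origin in Clinical data collection. Either choice restores coherence:

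- **Diagnosis for both.** This matches the follow-up described under Study design. Add that each child enters the risk set at enrollment (delayed entry), so that time before enrollment is not counted as event-free.
- **Enrollment for both.** The earlier interval is then not counted and no delayed entry is needed.

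The cost is one line of definition and, with diagnosis as origin, an entry time in the survival code. The article lists no date fields, but its two definitions already need both the diagnosis and the enrollment date. Confirm that both are in the database. Analysis is planned for study completion, so the change can be made before any survival result exists. No sample size or power statement needs revision on this account.
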